### Recruitment

A recent study estimated the population-based prevalence of CAS in children aged 4 to 8 years to be 1 child per 1000 [24]. Given that there were about 303,000 children between the ages of 5 and 9 years in Hong Kong in the mid-2020 [25], there may be 303 children in this age range in Hong Kong who are currently impacted by this severe motor speech disorder. Children were recruited through local advertising and invitations. Recruitment posters were posted in the university campus and on the web via social media platforms. The digital version of the posters was posted on the official Facebook page of the university speech-language therapy clinic, the Facebook page and Instagram accounts of Cantonese CAS, and the personal Facebook and Instagram accounts of the members of the research team. For the CAS group, recruitment information was also delivered to speech-language pathologists who attended local continuing education seminars on Cantonese CAS. Personal invitations were sent to the parents of children with CAS who have connections with the research team. The non-CAS groups were recruited from the general public by forwarding the digital posters to the parents of preschool children on WhatsApp chat groups, inviting parents of the children who were receiving speech-language therapy services in the university clinic, and sending invitation emails to kindergartens located in the same district as the university.

### Procedure

#### Initial Assessment

An expert speech-language pathologist will conduct initial assessments to diagnose each participant, if appropriate. The expert speech-language pathologist will have at least 10 years of clinical experience in assessing and treating Cantonese-speaking children with and without CAS. The assessment tasks include case history, speech sample collection, standardized language tests (ie, Hong Kong Test of Preschool Oral Language [Cantonese] [26] and Hong Kong Cantonese Receptive Vocabulary Test [27]), standardized articulation test (ie, Hong Kong Cantonese Articulation Test [28]), imitation of polysyllabic words, a standardized tone identification test (ie, Cantonese Tone Identification Test [29]), an oral and speech motor control assessment [30], and the documentation of prosodic characteristics. If a child is suspected to have autism spectrum disorder (ASD), the expert speech-language pathologist will conduct further assessments. According to Tierney et al [31], there is high comorbidity between CAS and ASD. The diagnosis of CAS and ASD may be delayed or inaccurate when both conditions are present in a child; children with CAS may be wrongly diagnosed with ASD and vice versa. Therefore, the Autism Diagnostic Observation Schedule, Second Edition [32], a standardized tool with high specificity and sensitivity for diagnosing ASD [33], will be administered to obtain information about the appropriateness of an ASD diagnosis. The assessment session will be audio- and video recorded so that another expert speech-language pathologist can review the assessments and diagnose independently. The CAS diagnosis will be confirmed if both speech-language pathologists reach a consensus on the presence of CAS features.

The diagnosis of CAS will be confirmed based on international standards and the methods used in our previous pilot study [20]. A CAS diagnosis will be based on the presence of 3 consensual features [1] and 4 clinical features that have reported 91% diagnostic accuracy [22], with appropriate modifications for Cantonese-speaking children, and across different assessment tasks (eg, speech sample, imitation of polysyllabic words, standardized articulation test, and diadochokinetic tasks). Murray et al [22] suggest using (1) syllable segregation, (2) lexical stress matches, (3) percent phonemes correct from polysyllabic words, and (4) articulatory accuracy on repetitions of [pʌtʌkʌ] for the differential diagnosis of CAS. Modification of some of these features is necessary for Cantonese. The second feature will be changed to *lexical tone errors* owing to the prosodic differences between English and Cantonese. The third feature will be changed from both segmental and suprasegmental correctness to only segmental correctness because of the constant duration of Cantonese syllables [34]. This set of criteria was used in our previous pilot study [20].

#### MPT and SRT

Every child will perform the MPT, SRT, and TST. The order of administration will be randomized. The administrative procedures and interpretation of MPT and SRT are described in the studies by Rvachew et al [35] and Rvachew and Matthews [15], respectively. There are four tasks in the MPT, including (1) maximum phonation duration, (2) MFD, (3) maximum repetition rate for monosyllabic stimuli, and (4) MRRtri. A total of 6 scores can be obtained from these tasks [11]. A dyspraxia score of 0, 1, or 2 is obtained from the performances of MFD and MRRtri. A dyspraxia score of 2 indicates the presence of CAS in children.

The SRT includes 18 items [12]. The items are formed of early developing phones (eg, [m], [d], [n], and [a]), which are easier for younger or severely impaired children to produce. The items included eight 2-syllable stimuli (eg, [bada]), six 3-syllable stimuli (eg, [bamana]), and four 4-syllable stimuli (eg, [bamadana]). The SRT gives 4 scores, including a competency score, an encoding score, a memory score, and a transcoding score. The interpretation of these 4 scores is based on z-scores from the means and SDs reported in the study by Lohmeier and Shriberg [36]. Table 1 presents a comparison of MPT and SRT.

Most of the stimuli used in the MPT and SRT are shared between English and Cantonese. For example, the vowel [a] and initial consonants [m], [f], and [s] in the MPT and SRT are shared in Cantonese. Although the voiced consonants [b] and [d] and voiceless consonants [p], [t], and [k] in English cannot be found in Cantonese, these sounds can be replaced by voiceless unaspirated [p] and [t] and voiceless aspirated [p^h^], [t^h^], and [k^h^] in Cantonese. This replacement is logical as, from a motor perspective, the contrastive aspiration feature in Cantonese consonants is similar to the voicing feature in English consonants [38]. With this logical replacement, it is anticipated that the SRT and MPT will be useful in differentiating between Cantonese speakers with and without CAS, as has been proven in English and Dutch speakers [11,15].

**Table 1 table1:** Comparison of the maximum performance tasks (MPT) and Syllable Repetition Task (SRT).

	MPT [11]	SRT [12]
Area assessed	Motor planning and programming of speech	Encoding process (mapping) Memory process (prearticulatory or phonological planning) Transcoding process (transformation of the phonological plan into a motor plan)
Scores	MPD^a^: mean duration of the longest prolongation of [a] and [mama] MFD^b^: mean duration of the longest prolongation of [s], [f], and [z] MRRmono^c^ score: mean repetition rate for the fastest repetition of each [pa], [ta], and [ka] MRRtri^d^ score: number of syllables produced per second in the child’s fastest repetition of [pʌtʌkʌ] Sequence score: 1 for correct sequence and 0 for unsuccessful production Attempt score: number of attempts required to produce the correct sequence	Competency: PCC^e^ of 18 items Encoding: percentage of consonants within-manner class substitution errors (excluding voicing errors) Memory: ratio of PCC for 3-syllable items to PCC for 2-syllable items Transcoding: percentage of items that are produced with ≥1 additions
Interpretation of the scores	MFD and MRRtri scores are used to obtain a dyspraxia score (0, 1, or 2), while MPD and MRRmono scores are used to obtain a dysarthria score (0, 1, or 2)	Interpretation of these 4 scores is made based on the z-scores from the means and SDs reported in the study by Lohmeier and Shriberg [36]
Criteria of CAS^f^ diagnosis	A dyspraxia score of 2 indicates the presence of CAS; it is obtained when MRRtri ≤3.4 or Sequence=0 or Dyspraxia score is not 0 or 1	Cutoff scores for CAS diagnosis [37]: Competency score=65 Encoding score=46.9 Memory score=67.5 Transcoding score=80

^a^MPD: maximum phonation duration.

^b^MFD: maximum fricative duration.

^c^MRRmono: maximum repetition rate for monosyllabic stimuli.

^d^MRRtri: maximum repetition rate for trisyllabic stimuli.

^e^PCC: percentage of consonants correct.

^f^CAS: childhood apraxia of speech.

#### TST Procedure

The TST proposed in this study is a shorter version modified based on the findings in the study by Wong et al [18]. This new version of TST has 16 stimuli, derived from 2 vowel structures, 2 consonant-vowel structures with early acquired sounds, and 3 early acquired Cantonese tones. The details of the TST are listed in Table 2. There are twelve 1-syllable items and four 3-syllable items. Both word and nonword stimuli are included. The participants will repeat each item as fast as they can 5 times. Four outcome measures will be obtained from the TST:

Tone accuracy will be calculated from perceptual judgments of correctness.Tone consistency will be calculated using the consistency strength formula described in the study by Williams et al [19]. The 5 repetitions of each stimulus will be compared with the children’s own baseline one by one to determine the consistency strength of that production.F0 values will be measured using Praat. F0 will be estimated at 5 evenly spaced time points (0%, 25%, 50%, 75%, and 100%) from the beginning to the end of the voiced segment of each syllable in the TST [39].Acoustic durations will be measured in Praat from the onset of the first syllable to the end of the last syllable.

All assessment sessions will be conducted at a local university clinic or laboratory, and all data collection sessions will be conducted in the soundproof booth in the laboratory. Children’s performances on the MPT, SRT, and TST will be audio- and video-recorded. Two speech-language pathologists with experience in childhood disordered speech will perceptually transcribe children’s productions using narrow transcription and score their performance. Furthermore, 20% of the ratings will be rerated by the speech-language pathologists to determine intra- and interrater reliability.

**Table 2 table2:** Stimuli of tone sequencing task (TST) for the proposed study.

TST type	Structure	
	Vowel	Consonant-vowel

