### CAS Diagnosis in English-Speaking Children

The gold standard for making a CAS diagnosis primarily relies on perceptual judgments of CAS experts. However, very recently, a pilot study reported only moderate agreement among 4 expert listeners [10]. Along with perceptual judgment, the maximum performance tasks (MPT) [11] and Syllable Repetition Task (SRT) [12] have been reported to provide valuable relevant information about segmental sequencing skills in children with CAS. Both MPT and SRT assess deficits in speech processing. The MPT aims to assess motor involvement in children with speech problems [11]. Specifically, the maximum repetition rate for trisyllabic stimuli (MRRtri) and maximum fricative duration (MFD) in MPT assess underlying deficits in the motor planning and programming of speech [13], while the maximum repetition rate for monosyllabic stimuli and maximum phonation duration assess deficits in speech motor execution. The SRT targets encoding, memory, and transcoding processes, which refer to mapping, prearticulatory or phonological planning, and transformation of the phonological plan into a motor plan, respectively [14]. Although the terminology is not identical, both the MPT and SRT address the same underlying deficits of CAS, speech motor planning and programming skills. Research has shown that the MPT has high sensitivity and specificity (ranging from 89% to 100%) in making a CAS diagnosis [11], whereas a cutoff transcoding score of 80 on the SRT is able to differentiate children with CAS from children with concomitant speech delay and language impairment (LI) [15].

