### Strengths and Limitations

On completion, this study will provide 2 objective measures (ie, MPT and TST) and 2 measures that convert perceptual judgments into quantitative data (ie, SRT and TST) for diagnosing CAS in Cantonese speakers. The results will promote the standard of CAS diagnosis in Cantonese speakers from reliance on expert perceptual judgment based on a list of clinical features [41] to a combination of perceptual judgment and quantitative data. In addition, the short administration time of the measures proposed in this study (ie, approximately 15-20 minutes per measure) will provide clinicians with quick and accurate methods for CAS diagnosis in Cantonese speakers than approximately 2 hours of comprehensive assessment [18,41,42] of speech motor skills reported in the literature. Moreover, the results of this study will provide the basis for further investigations of pitch-variation skills in children with CAS who speak other tonal languages (eg, Mandarin, Vietnamese, and Thai) as well as in children with CAS who speak nontonal languages (eg, English). Finally, investigations of the effects of linguistic elements (such as the lexical status, syllable structure, number of syllables, and syllable position) on children’s pitch-variation skills or speech motor control will provide information on how the linguistic elements of Cantonese interact with speech motor planning and programming skills.

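### The article states no masking to group for the raters who score the index tests by ear, and does not separate them from the diagnosing experts

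*Protocol article*

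**What the plan says.** The article describes the study as a comparison of diagnostic accuracy (Study Design). On index-test scoring, TST Procedure gives four facts:

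- **Who and how:** "Two speech-language pathologists with experience in childhood disordered speech will perceptually transcribe" the productions in narrow transcription and score them.
- **From what:** the children's "performances on the MPT, SRT, and TST will be audio- and video-recorded".
- **With what check:** "20% of the ratings will be rerated by the speech-language pathologists to determine intra- and interrater reliability".
- **On what basis:** "Tone accuracy will be calculated from perceptual judgments of correctness". By contrast, "F0 values will be measured using Praat", and so are acoustic durations.

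Strengths and Limitations lists the SRT and part of the TST as measures that turn perceptual judgment into numbers.

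The diagnosis is covered under Initial Assessment. One expert diagnoses, a second reviews the recordings and diagnoses independently, and CAS is confirmed when they agree. The diagnostic features include lexical tone errors and accuracy in repeating [pʌtʌkʌ]. Under Statistical Methods, the index-test scores go into mixed models by group and into ROC curves that set cutoffs.

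**The concern.** In an accuracy study, the index test should be read without knowledge of the reference diagnosis. That matters most when the reading is a listener's judgment and the diagnosis rests partly on the same features. Both conditions hold here: a tone heard as wrong counts towards the diagnosis and also lowers the TST score. A failed [pʌtʌkʌ] sequence does the same for the MPT sequence score, which feeds the dyspraxia score in Table 1.

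If a rater knows that a child has CAS, borderline productions may be marked wrong more often. The error would favour the study's hypotheses. It would raise apparent sensitivity and specificity, widen group differences and affect the new cutoffs. It could also distort the comparison between tests, because perceptual scores are more open to it than instrumental ones. A larger sample would not remove it.

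**Working it through.** **1. Is masking stated anywhere?** The article states no figure on this point, so the first check is textual.

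| Place | Safeguard stated | Does it mask the index-test raters? |
|---|---|---|
| Initial Assessment | Second expert diagnoses independently | No; it protects the reference standard |
| MPT and SRT | Order of administering the tests is randomized | No; it concerns the child's session, not the scoring |
| TST Procedure | 20% re-rated | No; it measures agreement |
| Ethics Approval | Data kept confidential, identifying data removed | No; it concerns privacy and does not mention group |

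No section masks the raters or says that they took no part in the diagnosis.

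**2. Which scores are exposed?**

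- *Exposed:* TST tone accuracy, a direct judgment; tone consistency, through the transcription it is computed from; SRT scores, chiefly competency (percentage of consonants correct); MPT sequence score, a correct/incorrect call.
- *Direction less clear:* SRT memory is a ratio of two percentages, so proportionally stricter scoring cancels. SRT encoding is a percentage of one error type, so stricter scoring has no obvious direction.
- *Much less exposed:* F0 and duration from Praat, and the timed MPT scores.

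**3. What would re-rating show?** If rater A and rater B both mark CAS children down by the same amount, their agreement is unaffected. Good reliability on 20% of ratings is therefore compatible with a shared bias.

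**4. How large could the effect be?** The documents give no size for rater bias. I assume a net downward shift *b* of 0.2 to 0.5 SD for CAS relative to controls, with normal scores of equal variance. The true difference *d* is taken from the pilot tone-accuracy range of 1.37 to 1.98 (Previous Pilot Studies), treated as free of rater bias.

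AUC = Φ((d + b)/√2). Sensitivity = specificity = Φ((d + b)/2) at the Youden cutoff.

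| d | b | (d + b)/√2 | AUC | Sensitivity = specificity |
|---|---|---|---|---|
| 1.37 | 0 | 0.969 | 0.834 | 0.753 |
| 1.37 | 0.2 | 1.110 | 0.867 | 0.784 |
| 1.37 | 0.5 | 1.322 | 0.907 | 0.825 |
| 1.98 | 0 | 1.400 | 0.919 | 0.839 |
| 1.98 | 0.2 | 1.541 | 0.938 | 0.862 |
| 1.98 | 0.5 | 1.754 | 0.960 | 0.893 |

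**5. Limiting case with no true difference.** With d = 0, AUC goes from 0.50 to Φ(0.2/√2) = 0.56 and Φ(0.5/√2) = 0.64. For a two-group test of 25 CAS children against 75 controls (Participants), two-sided 0.05, the standardized shift is b/√(1/25 + 1/75) = 4.33b. The chance of a significant result in the expected direction is Φ(4.33b − 1.96): about 14% at b = 0.2 and 58% at b = 0.5. The pilot data suggest a real difference, so this case only marks the edge of the range.

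**The case against.** The strongest reply is that the article is silent, and silence is not a plan to score unmasked. It is a condensed report, and the handling of coded files might be described elsewhere. The two roles are also worded differently: diagnosing experts need at least 10 years with Cantonese-speaking children, while transcribers need experience in childhood disordered speech. They may well be different people. This stands as far as it goes. A reader might infer that raters will know the group, or that the same experts will diagnose and score; the text supports neither. But the article does give the raters, the medium and the reliability check, and it states independence for the second diagnostician. Masking of index-test readers bears directly on the validity of the accuracy estimates, so its absence from this description is more than a missing detail.

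Two other inferences go too far:

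- The introduction reports "only moderate agreement among 4 expert listeners". That concerns expert diagnosis of CAS. It does not show that transcription or tone scoring is equally uncertain.
- Under Recruitment, "Personal invitations were sent to the parents of children with CAS who have connections with the research team". This makes some families known to the team, but nothing says that the transcribers are the team members concerned.

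The timing is also open. The article does not say whether the two experts reach consensus before or after the index tests are scored, so a rater might have no confirmed label to know.

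On size, two of the three control groups also have speech disorders. Raters may expect errors there too, which would shrink the net shift. Finally, masking cannot be complete, because the speech itself may suggest the group. None of this removes the gap; it limits what can be claimed about its effect.

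**Conclusion.** The point holds as a gap in a stated procedure: no masking to group is described for the raters of the perceptual index-test scores, and nothing keeps them apart from the diagnosing experts. Because diagnosis and index tests share features, knowledge of the diagnosis can inflate sensitivity, specificity and group differences on those scores. It does not follow that bias will occur, or that the Praat and timed measures are affected to a similar degree.

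The gains in AUC over the pilot range are about 0.03 to 0.07 at d = 1.37 and 0.02 to 0.04 at d = 1.98. They rest wholly on the assumed shift of 0.2 to 0.5 SD, on normal scores of equal variance, and on pilot effect sizes from a sample that the article itself calls extremely small.

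**What to change.** Add to TST Procedure that the perceptual measures (SRT, TST tone accuracy and consistency, MPT sequence score) are scored from audio files labelled only with a study code and presented in random order across groups. The planned raters have no access to group, recruitment source or the initial-assessment file. No rater scores a child whom he or she diagnosed. Recordings already made can be scored in the same way. If this is already the practice, a sentence saying so closes the point.

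The cost is renaming and shuffling files, with the same raters and recordings. Raters lose the visual cues of the video, and masking stays partial for the reason given above.

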**TSTmono^a^**		
	[a1^b^]^c^×5	[pa1]^c^×5
	[a2^d^]^c^×5	[pa2]^c^×5
	[a4^e^]^c^×5	[pa4]^c^×5
	[u1]×5	[hu1]×5
	[u2]×5	[hu2]×5
	[u4]×5	[hu4]×5
**TSTtri^f^**		
	[a1a2a4]×5	[pa1pa2pa4]×5
	[u1u2u4]×5	[hu1hu2hu4]×5

^a^TSTmono: tone sequencing task for monosyllabic stimuli.

^b^The number 1 indicates high-level tone in Cantonese.

^c^Indicates word stimuli (the others are nonword stimuli).

^d^The number 2 indicates high-rising tone in Cantonese.

^e^The number 4 indicates low-falling tone in Cantonese.

^f^TSTtri: tone sequencing task for trisyllabic stimuli.

### Statistical Methods

For the statistical analysis, linear mixed-effects models will be used. Our models will include group (CAS vs SSD vs S&LI vs TD) as a fixed effect and participants and items as random effects.

The sensitivity and specificity of the MPT, SRT, and TST in making a diagnosis of CAS in Cantonese-speaking children will be determined using the receiver operating characteristics curve [40]. The new cutoff scores of the MPT and SRT to diagnose CAS in Cantonese-speaking children will be compared with the existing cutoff scores recommended for English-speaking children. The cutoff scores for the TST will also be determined from the receiver operating characteristics curve.

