### Previous Pilot Studies

A recent study [14] identified a new clinical feature, namely tone production errors, which has not been reported in English speakers with CAS. The authors proposed that the same underlying deficit of speech motor planning and programming skills manifests differently in Cantonese and English [14]. Both English and Cantonese speakers with CAS may have similar control challenges with the correct production of segments; however, they control suprasegmentals differently because of linguistic differences. Suprasegmentals are overlaid differently for lexical stress in English versus lexical tone in Cantonese. English speakers apply 3 stress features—simultaneous pitch, loudness, and duration variations—to syllables to express a grammatical or pragmatic meaning. Cantonese speakers vary the pitch of segments to indicate different lexical meanings. Owing to these differences, further investigations of lexical tone errors are vital to increase the understanding of tone production skills in children with CAS.

In an effort to further explore tone production skills in Cantonese-speaking children with CAS, tone sequencing tasks (TSTs) have been used in 2 studies to examine the accuracy, consistency, and duration of tone production in Cantonese-speaking children with CAS [17,18]. The TST is considered to be a potential assessment task that reflects impairment in speech motor planning and programming in Cantonese-speaking children with CAS [17,18]. It requires children to produce 5 repetitions of each item that is formed of 3 early-acquired Cantonese tones, that is, tone 1 (high-level), tone 2 (high-rising), and tone 4 (low-falling). Wong et al [18] administered the initial version of the TST to 2 Cantonese-speaking children with CAS and 2 Cantonese-speaking children with non-CAS SSDs. The results showed that children with CAS performed significantly more poorly than children without CAS in sequencing tones. The effect sizes (Cohen *d*) for tone accuracy and consistency were 0.68 and 0.60, respectively. Both of them were considered to be medium-to-large effect sizes.

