In a subsequent study, the research team examined the linguistic effects of syllable structure and lexical status on TSTs using the second version of the TST [18]. A total of 4 Cantonese-speaking children with CAS were matched with 3 children with non-CAS speech and LI (S&LI), 3 with LI alone, and 3 with typical development (TD). Tone accuracy was judged perceptually and calculated as the percentage of tones correct. The consistency strength procedure adopted from the study by Williams et al [19] was used to calculate consistency scores. In the study by Wong et al [20], the team added 2 acoustic measures (ie, fundamental frequency [F0] values and acoustic duration) to further examine the data. The results showed both syllable structure and lexical status effects. Cantonese-speaking children with and without CAS showed significant between-group differences in F0 values for both vowel and consonant-vowel structures, as well as tone accuracy, tone consistency, and acoustic duration of word stimuli. A small to medium effect size (Cohen *d* ranging from 0.22 to 0.61) was obtained for F0 values, whereas large effect sizes were obtained for tone accuracy (Cohen *d* ranging from 1.37 to 1.98), tone consistency (Cohen *d* ranging from 1.36 to 1.85), and acoustic duration (Cohen *d* ranging from 0.9 to 1.45). The results suggest that syllable structure and lexical status play some roles in tone sequencing skills in children with CAS. In summary, these pilot studies suggest that children with CAS have difficulty with pitch-variation skills, specifically tone sequencing skills, and perform more poorly than control groups. The findings also support the diagnostic potential of TST as it provides a platform to investigate pitch variation in children with CAS and should be further developed as a linguistically appropriate assessment tool for Cantonese-speaking children. However, the generalizability of these findings is limited because of the extremely small sample sizes.

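### Tone accuracy is to be analysed with a linear mixed model; if controls score near ceiling and children with CAS score lower, the usual single-variance form understates the standard errors of the CAS contrasts

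*Protocol article*

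**What the plan says.** Statistical Methods gives one model family for group comparisons: "linear mixed-effects models will be used". Its terms follow: "Our models will include group (CAS vs SSD vs S&LI vs TD) as a fixed effect and participants and items as random effects". No outcome is named, no exception is made, and no link function or variance structure is given.

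TST Procedure lists four outcomes: tone accuracy, tone consistency, F0 values and acoustic duration. On the first it says: "Tone accuracy will be calculated from perceptual judgments of correctness". In the pilot (Previous Pilot Studies) the same outcome was a percentage: "Tone accuracy was judged perceptually and calculated as the percentage of tones correct".

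The tones were selected as "3 early-acquired Cantonese tones". Comparison With Prior Work predicts a lower percentage correct in CAS than in the control groups. Participants says that the original sample size was derived from the pilot effect size for tone accuracy. No section gives an accuracy level or spread for any group.

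**The concern.** F0 and duration are continuous, and a linear mixed model is a natural choice for them. Tone accuracy is different. With items as a random effect, the data enter at item or repetition level, where each value is binary or a coarse proportion. Whatever the level, the spread of a bounded percentage depends on its mean and narrows towards 100%.

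The study expects the groups to differ in mean. If typically developing children, and perhaps other controls, are close to 100% on early-acquired tones while children with CAS are well below, the child-to-child spread will differ strongly between groups. A model with one child variance and one residual variance averages those spreads. The averaged error is too small for contrasts involving the more variable group and too large for contrasts among near-ceiling groups. At stake is Hypothesis 2 (poorer pitch-variation skills in CAS than in controls) on one of its outcomes: intervals for CAS versus control would be too narrow and p-values too small.

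**Working it through.** **The plan's own figures.** The plan prints no standard error or accuracy level to reproduce. Its one calculation tied to tone accuracy is the original power statement; the critical value F(3, 168) = 2.658 reproduces exactly, but it does not bear on this point.

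**Inputs from the article.** 25 children per group, four groups. "This new version of TST has 16 stimuli", of which 12 have one syllable and 4 have three. "The participants will repeat each item as fast as they can 5 times". Tones per child: (12 × 1 + 4 × 3) × 5 = 120.

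**Assumed inputs.** CAS 70% correct; the three control groups at one common level, varied from 70% to 98%; child effects normal on the logit scale with SD 1; no item effects.

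**Formula.** In a balanced design, the linear mixed model's group contrast has the same standard error as a one-way ANOVA on the child means. Let vC and v0 be the variances of a child's percentage correct in CAS and in each control group.

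- Model variance of CAS minus control: 2 × [(vC + 3·v0)/4] / 25.
- True variance: (vC + v0) / 25.
- SE ratio, model to true: √[(vC + 3·v0) / (2(vC + v0))].

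The ratio is 1 when vC = v0 and falls towards √0.5 = 0.71 as v0 goes to zero. Numerical integration of the assumed logit-normal distribution, plus binomial error on 120 tones, gives vC = 0.0345. Coverage is from 20,000 simulated trials.

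| Controls correct | v0 | SE ratio, CAS vs control | Coverage of 95% interval |
|---|---|---|---|
| 70% (same as CAS) | 0.0345 | 1.00 | 95% |
| 80% | 0.0226 | 0.95 | 94% |
| 90% | 0.0090 | 0.84 | 90% |
| 95% | 0.0031 | 0.76 | 86% |
| 98% | 0.0007 | 0.72 | 84% |

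Example at 90%: √[(0.0345 + 0.0269) / (2 × 0.0435)] = √0.706 = 0.84.

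**Tied to the pilot effect size instead.** CAS accuracy was set so that Cohen d against controls equals the pilot's 1.37 to 1.98, with child logit SD 0.7 to 1.5. The ratio is 0.96-1.10 with controls at 60-70%, 0.91-0.94 at 80%, 0.82-0.86 at 90%, 0.76-0.81 at 95% and 0.72-0.78 at 98%.

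**False positives when a second group is as low as CAS.** Take CAS and S&LI truly equal at 70%. The linear model rejects equality at nominal 5% in about 15% of trials with the other two groups at 96%, about 12% at 90% and about 8% at 80%. A contrast using the two groups' own variances stays at about 5% throughout.

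**Do the remedies work?** With accuracy 70/95/95/97% (CAS/SSD/S&LI/TD) and logit SD 1, coverage over 400 trials is 84-87% for CAS contrasts under the linear model, 93-95% under a binomial mixed model and 94-96% under a linear analysis with group-specific variances. The binomial model needs one safeguard. With CAS = S&LI at 70% and the others at 96%, likelihood-ratio tests (800 trials) reject the true null as follows.

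| Logit SD: CAS and S&LI / SSD and TD | Binomial, one common child variance | Binomial, group-specific child variance |
|---|---|---|
| 1.0 / 1.0 | 5.1% | 5.5% |
| 1.5 / 1.0 | 8.6% | 5.9% |
| 1.5 / 0.7 | 11.1% | 5.9% |

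**The case against.** A reader might infer that the standard errors for tone accuracy are simply wrong because the outcome is binary. The documents do not support that. No accuracy figure is given for any group, and near-ceiling performance is inferred only from the tones being acquired early. The same task asks for fast repetition, includes nonwords and is given to children from 3 years of age, so controls may score well below ceiling. With controls at 80% the error is small, and with equal levels there is none. The cause is variance that differs between groups, not binary data as such. This part of the objection stands and makes the point conditional.

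It can also be said that a linear mixed model with group-specific variances is still a linear mixed model, and that an article may leave variance structure to a fuller plan. That is fair as far as it goes, and such a model is accepted below as an alternative. But the article does fix a linear model for every outcome without exception, and the form normally fitted under that description has common variances.

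Two further inferences should be resisted. Loss of power for SSD versus TD can be large in such simulations, but no stated hypothesis concerns that contrast. Nor does the article rank CAS versus S&LI above CAS versus SSD; Participants gives a reason for each. Finally, Statistical Methods does not name tone accuracy. Its inclusion follows from the general wording and from there being no other group model.

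**Conclusion.** The point holds conditionally and deserves a change. The stated model does not suit one stated outcome. If controls are at 90-98% correct and CAS is near 70%, CAS-versus-control standard errors come out 16-28% too small (ratios 0.84 to 0.72) and nominal 95% intervals cover about 84-90%. At 80% in controls the shortfall is about 5%; at equal levels it is nil. These sizes rest on assumed accuracy levels, an assumed child spread, balanced groups of 25 and no item effects. The consequence is limited to Hypothesis 2 on tone accuracy. F0 and acoustic duration are not touched by this argument, and Hypotheses 1 and 3, which rest on ROC analyses, are not affected.

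**What to change.** In Statistical Methods, state that tone accuracy will be analysed with a binomial (logit-link) mixed model on single tone productions, with the same group fixed effect and the same participant and item random effects, and with the participant variance allowed to differ by group. A linear model with group-specific or robust variances is an acceptable alternative or check. Report odds ratios together with model-based percentages correct. Keep linear mixed models for F0 and acoustic duration.

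The cost is a sentence or two, with no new data. Effects on the odds scale must be back-transformed for clinical readers, and a few more variance parameters must be estimated from 25 children per group.
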